**TRAINING**	
4. Formal facilitator training	4. 25 h. of face-to-face facilitator training for MBSR and 25 h. of training control groups with MBSR instructor and PI with 22 and 12 years of experience, respectively
5. New facilitator monitoring	5. PI and MBSR consultant will provide weekly 1.5 h. group supervision + 30 min. of individual supervision
**DELIVERY**	
6. Electronic recording of program sessions	6. Research coordinator will monitor web-app delivery; all inquiry discussions will be recorded and saved
7. Program sessions reviewed and rated	7. Interventions will be delivered via the same format across the two groups; facilitators will discuss weekly group-based participant feedback at supervision
8. Facilitator supervision and feedback	8. PI and MBSR consultant will provide weekly 2-h supervision (group + individual) with new facilitators to ensure standardized delivery
**RECEIPT**	
9. Participant attendance	9. Participant attendance and meta-data will be recorded; participants who miss sessions will receive call from facilitator
**ENACTMENT**	
10. Practice adherence	10. Participants' intervention engagement and homework completion will be recorded and monitored
11. Measurement of participant skill and strategy use in real-world settings	11. Participants' engagement level will be correlated with outcome measures
12. Dispositional mindfulness measures	12. Participants will complete mindfulness scales at pre- and post-intervention (e.g., MAAS)

Treatment fidelity reporting based on NIH Behavior Change Consortium (BCC) recommendations (Bellg et al., 2004) [91] and mindfulness intervention fidelity reporting adapted from Kechter, Amaro, and Black [92]

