Taken together, there is a growing recognition for the potential for mindfulness practices to improve attentional control—the biasing of task-relevant representations at the temporal, spatial, and response stages. However, this literature is still in its infancy, particularly in the evidence supporting mindfulness meditation as a tool for reducing age-related cognitive decline. The majority of studies, including our own pilot clinical trial, have had limited follow-up data, have relied on self-reported data for quantifying adherence to study materials, and did not include broad measures of transfer effects. This Phase I/II efficacy trial—HealthyAgers—aims to build on the existing literature by examining the immediate and longitudinal impact, relative to an active control group, of an eight-week mindfulness-based stress reduction (MBSR) program in improving attentional control and reducing mind-wandering in older adults. In addition, the control group in the study—Lifestyle Education (LifeEd) program—has been carefully designed to match the training group for non-specific factors that may influence the outcomes of interest. Participants in both groups will engage in a booster session every three months across the 12-month period following the intervention. Importantly, we have designed an in-house web/mobile application—HealthyAgers—to measure engagement with study materials for both groups to allow for careful assessments of dose–response relationships. We hypothesize that mindfulness training, compared to lifestyle education training, will improve attentional control and reduce mind-wandering. Secondary measures of this study will also assess the broad impact of mindfulness meditation for functional connectivity, fluid and everyday cognition, emotion regulation, and systemic inflammation. We hypothesize that mindfulness training will additionally result in an improvement in these secondary measures of healthy aging. The results of this study will establish the efficacy of this increasingly popular, low-cost intervention for older adults with regard to cognitive, affective, and neural health.

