### Primary outcome

The primary outcomes for this study are changes in measures of attentional control and mind-wandering during tasks of sustained attention. To quantify both attentional control and mind-wandering the following measures are being administered:

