### Study interventions

#### Mindfulness-Based Stress Reduction (MBSR) program

The MBSR program being offered in this study is modeled after the eight-week program developed and popularized by Jon Kabat-Zinn to reduce pain and stress [24]. The MBSR program is offered in a group setting wherein participants meet with trained facilitators once a week for two and a half hours each (except for the first class which is three hours) along with a four-hour retreat offered on a weekend (between weeks six and seven)—thus resulting in 24.5 h of face-to-face training. In these classes, facilitators cover a combination of experiential practices, didactics and teachings on the topics of mindfulness, and mindful movement exercises. These practices and teachings all center on cultivating present moment awareness in a framework that promotes acceptance and non-judgment. Moreover, the participants are provided with several opportunities to engage in small and large group-based discussions that offer a platform for social support, validation, and shared experiences. Supplementary Table 1 provides the agenda for each of the eight sessions of the MBSR program as well as the practices taught during the retreat. In addition to these classes, all participants are invited to engage in 30 min of formal homework practices, delivered through our web/mobile-based, in-house application that was named after the study—HealthyAgers. Working with a team of inter-disciplinary experts, including certified mindfulness experts, psychologists, wellness coaches, and computer programmers, we have carefully designed this iOS/Android mobile/web application to deliver and track guided meditation practices. This application will allow us to collect objective practice data on all our participants with the application providing information on minutes practiced, the frequency of engagement in mindfulness practices per week, and additional meta-data, including preferred practices, time of day preference, etc. After the eight weeks of the intervention, participants will be invited to continue engagement with mindfulness practices on their own, five times per week, for 12 months with two-hour, group-based booster sessions provided by the study facilitators every three months. Prior to the pandemic, all intervention sessions were provided in our group psychotherapy rooms housed in the Department of Psychology. Sessions shifted to the Zoom platform in March 2020 and continue to be offered virtually.

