After preprocessing of behavioral and neuroimaging data, all data will first be tested for normality, outliers, and errors. We will then compute summary statistics and compare groups’ baseline demographic and clinical characteristics; although randomization should balance the groups with respect to these characteristics, with a finite sample size, there may be some residual imbalance. Particular attention will be paid to characteristics that may be associated with outcomes (e.g., education, depression scores) as chance imbalance in these characteristics may confound the intervention effects. All statistical analyses conducted as part of the trial will be intent-to-treat. The primary outcome variables for this study are indices of attentional control and mind-wandering. To examine the immediate effects of mindfulness training, we will use a linear mixed model to account for the within-subject correlation arising from measuring each subject at two timepoints. Group (MBSR, LifeEd), Time (pre and post-training), and the Group X Time interaction will be defined as fixed effects, with covariates, when applicable (e.g., those identified as randomly differing between groups) included as fixed effects. Each participant’s intercept will be included as a random effect. To determine the maintenance effects of mindfulness meditation, we will construct a separate mixed linear model examining the long-term efficacy of mindfulness meditation with Time (pre-training, 6-month follow-up, and 12-month follow-up), Group (MBSR, LifeEd), and the Group X Time interaction effects. Secondary factors of functional connectivity, fluid and everyday cognition, emotion dysregulation and inflammation will also be examined by constructing linear mixed models.

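### The planned correlation of self-chosen engagement with outcomes cannot support a dose-response reading; use a within-arm, baseline-adjusted regression labelled exploratory

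*Protocol article*

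**What the plan says.** The Background introduces the study's web and mobile application as a way "to measure engagement with study materials for both groups to allow for careful assessments of dose–response relationships". Table 3 (fidelity components), Enactment, row 11 then states that participants' "engagement level will be correlated with outcome measures". The article names no other analysis of engagement. Row 11 mentions no adjustment, and it does not say whether scores or changes are correlated, or whether the arms are analysed separately.

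The amount of practice is the participant's choice. Under the MBSR program, "all participants are invited to engage in 30 min of formal homework practices" during the eight weeks, and afterwards "participants will be invited to continue engagement with mindfulness practices on their own". The application supplies "information on minutes practiced, the frequency of engagement in mindfulness practices per week", so the log is objective, but the dose is still self-selected.

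Two other statements bear on the point. Primary outcome: "The primary outcomes for this study are changes in measures of attentional control and mind-wandering". Data management and analysis: "All statistical analyses conducted as part of the trial will be intent-to-treat".

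**The concern.** A dose-response reading asks what would happen if the same person practised more. A correlation across people answers that only if those who practise more are otherwise comparable with those who practise less. People with better attention at entry, or more motivation, may well practise more and also test better later. The correlation then partly describes who they were.

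Nothing stated elsewhere in the article deals with this. The covariates in Data management and analysis belong to the mixed models and are chosen for imbalance between the arms, not for their relation to engagement. The expectancy analysis in the Discussion relates expectations to gains and is not described as an adjustment of the engagement analysis.

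At stake is the interpretation of a supporting result. Dose-response findings are easily quoted as support for causality, and the Background promises careful ones. There is also a conflict of wording: an analysis by amount of practice is not intent-to-treat, yet the article says that all analyses are.

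**Working it through.** The article gives no figure for the engagement analysis, so there is none to reproduce. The check asks how often a correlation would be significant when dose has no effect.

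**Inputs from the article.** 150 participants allocated 1:1 give 75 per arm. With the 25% drop-out allowed for in Sample size, 75 × 0.75 = 56 per arm. With the stated minimum of 130, 65 × 0.75 = 49. Alpha is 0.05, taken here as two-sided.

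**Assumed inputs, not in the article.** Correlation of baseline score with engagement 0.3 (range 0.2 to 0.4); correlation of pre- with post-training score 0.7 (range 0.6 to 0.8). Outcomes are oriented so that higher is better.

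**1. Raw post-training score**
- Spurious r = 0.3 × 0.7 = 0.21.
- Fisher z = atanh(0.21) = 0.213. At n = 56, 0.213 × √53 = 1.55.
- Chance of p < 0.05: Φ(1.55 − 1.96) ≈ 0.34. At n = 75 it is 0.44.
- Over the assumed ranges at n = 56, r runs from 0.12 to 0.32 and the chance from 14% to 68%.

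**2. Change score, same inputs**
- Spurious r = (0.21 − 0.30) / √(2 − 2 × 0.7) = −0.09 / 0.775 = −0.12.
- At n = 56 this is significant in about 14% of trials, in the wrong direction. It would also pull a real positive dose effect towards zero.

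**3. Regression on engagement and the pre-training score, same inputs**
- Standardized engagement coefficient = (0.21 − 0.3 × 0.7) / (1 − 0.3²) = 0. The bias disappears if engagement depends only on the measured baseline score.

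**4. A less favourable model, by simulation**

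Here engagement depends on underlying ability, which the baseline test measures with error, and/or on motivation. Assumptions: test-retest correlation 0.7; each correlates 0.3 with engagement where it operates; motivation affects the post-training score by 0.3 baseline SD; 4,000 runs per setting. Rejection rates at n = 56 with no dose effect:

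| Source of confounding | Raw post | Change | Adjusted for pre-score | Pre-score and motivation |
|---|---|---|---|---|
| Ability only | 47% | 5% | 12% | 12% |
| Motivation only | 10% | 12% | 13% | 5% |
| Both | 72% | 12% | 36% | 13% |

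For ability only, with its correlation with engagement at 0.2 to 0.4, the raw rate runs from 23% to 72% and the pre-score-adjusted rate from 8% to 20%. Where motivation is involved, the change-score rate runs from 11% to 15% over n = 49 to 75.

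The 34% in step 1 and the 47% here differ because of the model. When the 0.3 applies to underlying ability, the spurious r is 0.3 × √0.7 = 0.25 instead of 0.21.

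**The case against.** The strongest case against has five parts.

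- **Row 11 is a fidelity item, and a condensed article leaves detail to the full protocol or analysis plan.** This is partly right: covariates or analysis by arm may be specified elsewhere. But the row names a method, and it is the only one in the article that could serve the dose-response purpose announced in the Background.
- **The primary outcomes are defined as changes.** This stands and matters. On change scores stable ability does not create a false positive dose-response: the spurious correlation is about zero or negative, depending on the model. A reader might infer that the plan will pass off carried-forward baseline ability as a dose effect. That needs raw scores, which the article does not specify. The motivation route remains.
- **The magnitudes are assumed.** This stands. Eligibility also requires interest in mind–body interventions and commitment to the homework, which may narrow the spread in motivation.
- **Pooling is not stated.** This stands. MBSR logs meditation; LifeEd logs stretching, reading and videos. A pooled correlation would have no common dose meaning, but nothing says the arms will be pooled.
- **Adjustment does not cure the problem, and LifeEd is not inert.** This also stands. LifeEd covers physical and cognitively stimulating activity, so its engagement slope may reflect real effects as well as motivation.

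**Conclusion.** The point holds as a fault in a supporting analysis. The article ties self-chosen engagement to dose-response and names only a simple correlation to assess it. Confounding follows from the document; its size and sign do not. Under the assumed 0.3 and 0.7 with 56 per arm, the effect ranges from about 34% false positives on raw scores to a correlation of about −0.12 on change scores, with roughly 12% false positives on change scores when motivation is at work.

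A reader might infer that the efficacy conclusion is at risk. It is not: that rests on the Group by Time term in the randomized comparison and, for mind-wandering, on agreement of probes and response-time variability. Neither uses engagement. The change is worth making because it is cheap and the promise of dose-response is explicit.

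**What to change.** Replace the correlation in row 11 with a regression of the post-training outcome on app-logged engagement over the eight weeks, fitted within each arm. Adjust for the pre-training score, age, education, the randomization strata (sex, cognitive status, MRI eligibility) and the expectancy measure. Expectancy is taken at the end of the first session, so it follows randomization, and it is only a proxy for motivation. It will therefore remove less bias than the last column of the table suggests.

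Report the Engagement by Group contrast as a supportive comparison, not a clean negative control. State that the analysis is exploratory and observational, and exempt it by name from the sentence that makes all analyses intent-to-treat.

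The engagement logs, baseline scores, strata and expectancy measure are already part of the study, so no visits or participant burden are added. The cost is slightly more analysis work and probably a less favourable-looking association. Residual confounding will remain, and the report should say so.

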#### Assessing and maximizing adherence

Our lab has successfully conducted two RCTs on mindfulness training, and for both those studies, we have had adherence rates of ~ 80% (Whitmoyer et al., 2020; Schirda et al., 2020). In the current study, we will implement a number of strategies that have been successful in the past to promote adherence to the intervention as well as the assessment sessions. First, as both groups in the study will engage in training that promotes and discusses healthy aging, advertising the study as a trial on mind–body interventions for healthy aging will help recruit individuals with a genuine interest in making these changes. Second, detailing the study requirements in the recruitment materials, particularly the 30 min of daily practice for eight weeks, appears to have a positive influence on adherence to homework practices and retention rates. All our advertisement materials detail this time commitment on behalf of the participants. Third, once participants are enrolled in the study, weekly attendance at the online sessions is being monitored by course facilitators and communicated to the study coordinator. For every missed session, the study coordinator connects with the participant, and either schedules them for an individual appointment with the course facilitator or sends them a summary from the missed session. For participants who wish to not continue with the intervention, every attempt will be made to complete the assessment sessions.

### Data management and analysis

All study data (with the exception of blood samples) are being stored in the PI’s laboratory located in the Psychology Building at Ohio State. The laboratory is only accessible to approved personnel. Hard data files (e.g., consent forms, neuropsychological assessment data) are stored in locked cabinets inside the laboratory, whereas electronic data files (e.g., behavioral data, self-report questionnaires, neuroimaging data) are stored on a password-protected laboratory server. De-identified participant blood samples are stored at the Clinical Research Center at The Ohio State University.

Cognitive screening data will be coded by two independent research assistants in the lab with coder disagreements resolved by an experienced research assistant. Participants’ performance scores from the Conner’s Continuous Performance Test and the National Institute of Health Toolbox Cognition battery are automatically generated from each program and will then organized on the laboratory server via manual procedures and/or custom lab scripts. Participant’s behavioral data from the Go/No-Go, Emotion Regulation Choice, Gradual-Onset Continuous Performance Task, and the N-back task will be organized and coded by two independent laboratory members using custom scripts. Neuroimaging data quality will be assessed using a validated quality control pipeline [69] prior to conducting pre-processing. Pre-processing of the neuroimaging data will be conducted by either a postdoctoral researcher or an advanced graduate student in the lab with extensive training in neuroimaging analyses. All remaining processing and coding of neuroimaging data will be completed by two independent graduate students/postdoctoral researchers. Markers of inflammation from participant’s blood samples will be processed by the Clinical Research Center at The Ohio State University.

After preprocessing of behavioral and neuroimaging data, all data will first be tested for normality, outliers, and errors. We will then compute summary statistics and compare groups’ baseline demographic and clinical characteristics; although randomization should balance the groups with respect to these characteristics, with a finite sample size, there may be some residual imbalance. Particular attention will be paid to characteristics that may be associated with outcomes (e.g., education, depression scores) as chance imbalance in these characteristics may confound the intervention effects. All statistical analyses conducted as part of the trial will be intent-to-treat. The primary outcome variables for this study are indices of attentional control and mind-wandering. To examine the immediate effects of mindfulness training, we will use a linear mixed model to account for the within-subject correlation arising from measuring each subject at two timepoints. Group (MBSR, LifeEd), Time (pre and post-training), and the Group X Time interaction will be defined as fixed effects, with covariates, when applicable (e.g., those identified as randomly differing between groups) included as fixed effects. Each participant’s intercept will be included as a random effect. To determine the maintenance effects of mindfulness meditation, we will construct a separate mixed linear model examining the long-term efficacy of mindfulness meditation with Time (pre-training, 6-month follow-up, and 12-month follow-up), Group (MBSR, LifeEd), and the Group X Time interaction effects. Secondary factors of functional connectivity, fluid and everyday cognition, emotion dysregulation and inflammation will also be examined by constructing linear mixed models.

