## Methods/design

### Study design

The proposed study is a single-blind, randomized controlled trial (RCT) designed to examine the differential impact of mindfulness training compared to a lifestyle education group (LifeEd) on behavioral and neural measures of attentional control and mind-wandering. Secondary assessments involve measures of fluid cognition, everyday cognition, emotion regulation, and systemic markers of inflammation. One hundred fifty older adults (65–85 years old) are being recruited for the study and randomized to either an eight-week MBSR group or an eight-week LifeEd control group. Behavioral, neuroimaging, and inflammation data will be conducted at baseline prior to randomization and again at the conclusion of the eight-week intervention. Further, participants will be followed for an additional 12 months, during which time booster sessions will be provided once every three months, with cognitive and affective assessments performed at 6-month and 12-month follow-ups. Neuroimaging and inflammation data will only be collected at the 12-month follow-up. Figure 1 illustrates a timeline of study participation.

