### Randomization

Eligible and consenting participants will be randomized after completing baseline assessments to one of two groups: MBSR or LifeEd. A random permuted-block design (blocks of size 2 and 4) will be used, and the randomization with an allocation ration of 1:1 will be stratified by sex assigned at birth (male, female), cognitive status (cognitively normal, MCI), and MRI eligibility (eligible, not eligible) to ensure balance across these important factors. The biostatistician on the team, [name], prepared and maintains the randomization sequence for the eight strata. The project coordinator has been given concealed envelopes and only after a participant completes all pre-assessment sessions and is deemed eligible for the study does the project coordinator open the envelope from the respective stratum and assign the participant to either the MBSR or the LifeEd group. The project coordinator, the study facilitators and supervisors, and the study biostatistician will be the only members of the team who will be unblinded to group assignment. All personnel conducting assessments, behavioral or neuroimaging, will remain blind to group assignment.

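### The two specified mixed models estimate a baseline group difference that randomization makes zero: valid and unbiased, but avoidably imprecise

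*Protocol article*

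**What the plan says.** The Data management and analysis section of the protocol article specifies a linear mixed model for the immediate effect: "Group (MBSR, LifeEd), Time (pre and post-training), and the Group X Time interaction will be defined as fixed effects". Each participant's "intercept will be included as a random effect". The stated purpose of the mixed model is to handle the "within-subject correlation arising from measuring each subject at two timepoints", so the pre-training score is part of the response. Further adjustment is limited to "covariates, when applicable (e.g., those identified as randomly differing between groups) included as fixed effects". Nothing requires a common pre-training mean or makes the pre-training score a covariate.

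The same section gives the maintenance analysis as a separate mixed model with Group, Time (pre-training, 6 months, 12 months) and their interaction. For secondary outcomes it says only that linear mixed models will be built, and lists no terms.

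Two sections place baseline before allocation. Under Study design, the assessments "will be conducted at baseline prior to randomization and again at the conclusion of the eight-week intervention". Under Randomization, participants "will be randomized after completing baseline assessments to one of two groups", and the envelope is opened only once all pre-assessment sessions are complete.

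**The concern.** A Group main effect, in a model whose first response is the pre-training score, lets the arms have different true means at baseline. Randomization after baseline rules that out: any observed gap is chance. The model therefore spends information estimating a quantity known to be zero, and the noise in that estimate passes into the Group X Time term.

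What is at stake is precision on the primary outcomes. The sample-size section aims for power just above 0.80, and the text closing the primary outcome section requires improvement on both attention tasks, and on both mind-wandering indices, before efficacy is concluded. Precision given up on one measure lowers the chance of meeting such a joint criterion.

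**Working it through.** **Plan's own figures.** The protocol states no figure for the precision of these models and no rho. The nearest number is the evaluable N of 103, used below only as a yardstick. It reproduces with f² = 0.088/(1 − 0.088) = 0.0965 and a noncentral F test with 2 numerator degrees of freedom (power 0.8004). With 1 degree of freedom, as for a two-arm, two-visit interaction, the required N is 84. That mismatch is a separate matter and does not affect what follows.

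**Inputs.** Two visits, 1:1 allocation and baseline before randomization come from the protocol. So does the 25% drop-out (Sample size), applied here to post-training scores. Assumed: equal variance σ² at both visits and in both arms; rho of 0.5 to 0.8 as the main range, 0.3 to 0.9 as the wider one.

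**Complete data, n per arm.**
- Group X Time as planned (difference in mean change): variance = (2σ²/n) × 2(1 − rho).
- Baseline-adjusted or common-baseline analysis: variance = (2σ²/n) × (1 − rho²).
- Ratio = (1 + rho)/2, so the variance saving is (1 − rho)/2 and the standard-error saving is 1 − √[(1 + rho)/2].

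**Post-training scores missing.** Let p be the fraction observed. The planned model still uses baseline-only participants, so it is no longer exactly a change-score analysis. Its variance is 2σ²[(1 − rho²)/(np) + (1 − rho)²/n], against 2σ²(1 − rho²)/(np) with a common baseline mean. The saving is p(1 − rho)/[(1 + rho) + p(1 − rho)]. With p = 0.75 and rho = 0.5: 0.375/1.875 = 20%. With rho = 0.8: 0.15/1.95 = 7.7%.

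| rho (assumed) | 2(1 − rho) | 1 − rho² | Variance saving, complete | SE saving, complete | Variance saving, 25% missing |
|---|---|---|---|---|---|
| 0.3 | 1.40 | 0.91 | 35% | 19% | 29% |
| 0.5 | 1.00 | 0.75 | 25% | 13% | 20% |
| 0.6 | 0.80 | 0.64 | 20% | 11% | 16% |
| 0.7 | 0.60 | 0.51 | 15% | 8% | 12% |
| 0.8 | 0.40 | 0.36 | 10% | 5% | 8% |
| 0.9 | 0.20 | 0.19 | 5% | 2.5% | 4% |

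**Simulation check (65 per arm, complete data).** The fitted mixed-model interaction matched the difference in mean change to within 1e-15. ANCOVA reduced the variance by 24% at rho 0.5 and 9% at rho 0.8, against 25% and 10% in theory.

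**Maintenance model.** With complete data and the equal correlations implied by a random intercept, the saving at each follow-up visit is again (1 − rho)/2.

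**Scale for power.** Suppose, for illustration, that the planned contrast had 80% power at N = 103, two-sided alpha 0.05. Dividing 1.960 + 0.842 by √0.75 and subtracting 1.960 gives 1.275, about 90% power. With √0.90 it gives 0.993, about 84%. Equivalently, 80% power would need 103 × 0.75 = 77.25, so 78 evaluable participants, or 103 × 0.90 = 92.7, so 93.

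**The case against.** The strongest reply is that the planned model is standard, valid and unbiased under randomization, so preferring another estimator is a matter of taste. The first half stands: this is inefficiency, not error. The second does not. The protocol names the terms of the model, and the alternative uses data already collected and is more precise for every rho below 1.

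It may also be said that the covariate clause deals with chance imbalance. With complete two-visit data it cannot: a baseline covariate entered as a main effect cancels out of within-person change and leaves the Group X Time estimate as it was.

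Several stronger readings are tempting but not supported:
- **A fixed loss of 10% to 25% of precision.** This is a variance figure for complete data under an assumed rho. The document supplies no rho, and the saving is smaller on the standard-error scale and under the planned drop-out.
- **Bias through regression to the mean.** Chance baseline imbalance is the source of the extra variance already counted, not a second defect. Over randomizations the estimate is unbiased.
- **An underpowered trial.** This is not shown. The planned 150 less 25% leaves about 112 (150 × 0.75 = 112.5), above the stated 103.
- **A flaw stated for every outcome.** Only the two primary-outcome models list their terms. That the secondary models share the form is a reasonable inference, not a statement in the text.

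**Conclusion.** The point holds as an avoidable inefficiency in the immediate and maintenance models. Its direction does not depend on any assumption beyond rho below 1, but its size does. For the pre/post model the variance saving is 25% to 10% for rho 0.5 to 0.8 with complete data (about 13% to 5% in standard error or interval width), and about 20% to 8% with 25% of post-training scores missing. Over rho 0.3 to 0.9 with complete data it is 35% to 5%. All figures assume equal variances and 1:1 allocation. The change is worth making because it costs nothing; the planned result would not be invalid without it.

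**What to change.** Specify a constrained longitudinal model: one common pre-training mean for both arms, visit effects, and an explicit arm-by-visit term for each post-baseline visit, set to zero at baseline. Do not merely delete Group from the formula. With categorical Time, common software coding can then refit the same unconstrained model, so the equal-baseline constraint must be coded explicitly.

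A simple alternative for the immediate effect is an ANCOVA of the post-training score on arm with the pre-training score as covariate. The two are closely similar but not identical: a random-intercept model imposes equal variances across visits and ANCOVA does not, and they treat incomplete records differently. Name one as primary.

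Use the same constrained form for the maintenance model, with arm terms at 6 and 12 months, and for the secondary outcomes if they are to be modelled in the same way.

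The cost is analysis wording only, with no new data or visits. The article describes recruitment as ongoing; the change should be recorded before any unblinded analysis.
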